### Secondary objectives

To assess the proportion of patients with successful DR after 12 and 18 months, defined as using a lower dose than the standard dose and PASI ≤ 5.To assess differences in course of disease activity (PASI) and dermatology-related quality of life (DLQI) in patients with DR versus UC in 18 months.To assess and compare absolute PASI and DLQI scores at month 12 and month 18 in patients with DR versus UC.To assess the incidence of short disease flares (PASI > 5 at one time point) after 18 months in patients with DR versus UC.To assess the time until the first persistent flare (PASI > 5 for ≥ 3 months).To identify predictors for successful DR.To count and compare the number of serious adverse events (SAE) and adverse events of special interest (AEoSI) in patients with DR versus UC. AEoSI include, but are not limited to, infections, malignancies, and joint complaints or new-onset psoriatic arthritis.To assess the pharmacokinetic profile of reduced biologics versus the standard dose.To assess if DR is cost-effective compared to UC.To assess the proportion of patients with initiation of other anti-psoriatic treatments during the study (intensive topical therapies, methotrexate, acitretin) in patients with DR versus UC.

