The proportion of patients with successful DR will be expressed using descriptive statistics. PASI and DLQI course throughout the study will be compared between the intervention and control groups using mixed methods analysis. All disease-activity scores (PASI) will also be directly compared at each time point (every 3 months) between the two groups using an unpaired *t* test or a non-parametric alternative. PASI and DLQI at 12 and 18 months will be analyzed with ANCOVA in which the baseline values will be included as a covariate to gain efficiency. A multivariable regression analysis will be carried out in order to identify predictors for successful DR at month 12 and month 18. Possible candidate predictors will include baseline patient and treatment characteristics and baseline trough drug concentrations. Based on group size, we will test the four most promising variables. Proportions, rate ratios, and relative rate ratios, with corresponding confidence intervals, of SAEs and AEoSI will be described and differences between groups will be tested using classical statistical methods (Fisher exact test). SAEs and AEoSI *related to* DR will also be counted and expressed as proportions and rate ratios. A subanalysis for all outcomes will be made for the different drug classes and on individual drug level if appropriate (depending on numbers included per class).

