### Cost-effectiveness analysis

Cost-effectiveness of DR will be calculated based on health-status (SF-36), utilities measured with EQ-5D-5L, volumes of care (iMTA Medical Consumption Questionnaire), and loss of productivity and presenteeism (iMTA Productivity Cost Questionnaire). Utilities will be estimated by weighing the scored answers on the EQ-5D-5L with the local tariffs and using the trapezium rule quality-adjusted life years (QALYs) will be calculated. A sensitivity analyses will be conducted by calculating QALYs based on utilities from the SF6D system, derived from answers on the 12 specific SF-36 questionnaire answers. Cost prices for each volume of consumption will be determined based on standard local cost prices. Productivity losses will be valued by means of the friction cost method. Volumes of care will be multiplied with the cost prices for each volume of care to calculate costs. Because we anticipate non-inferiority of the DR strategy, cost-savings will be analyzed. Direct medical cost as well as total costs (medical and non-medical costs) will be compared between the intervention and control group. A possible small but acceptable loss of effect can be incorporated in the analyses by determining a decremental cost-effectiveness ratio (DCER) by dividing the difference in costs by the difference in quality-adjusted life-years (QALYs) between the groups. The DCER expresses with how much money a loss of 1 QALY is compensated. If this amount is high, decision-makers are willing to accept a loss of effect. Uncertainty in the DCER will be non-parametrically determined using bootstrap techniques (1000 replications). Results from this analysis will be presented in a scatter plot and willingness to pay (or accept) curve. Furthermore, the net monetary benefit (NMB) per patient will be calculated for different levels of willingness to pay (WTP) in dollars per QALY, using the formula: WTP * effect (difference in QALY) − costs. This results in the net amount of money saved, when the possible loss of QALY is corrected for, using different WTP levels per QALY.

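### Visit-wise PASI tests without baseline, and a QALY difference with no baseline-utility adjustment mentioned, give up precision that data already collected would supply

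*Protocol article*

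**What the plan says.** The protocol article, under Statistical analyses, gives three between-arm analyses of PASI:

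- Course over 18 months: "PASI and DLQI course throughout the study will be compared between the intervention and control groups using mixed methods analysis".
- Each visit, by t test with a nonparametric substitute allowed and no covariate named: "All disease-activity scores (PASI) will also be directly compared at each time point (every 3 months) between the two groups using an unpaired". This applies to PASI, not to DLQI.
- Months 12 and 18, for PASI and DLQI: ANCOVA, "in which the baseline values will be included as a covariate to gain efficiency".

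The Secondary objectives name the same two visits: "To assess and compare absolute PASI and DLQI scores at month 12 and month 18 in patients with DR versus UC".

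Under Cost-effectiveness analysis, EQ-5D-5L utilities are weighted with local tariffs and, "using the trapezium rule quality-adjusted life years (QALYs) will be calculated". The DCER is then obtained "by dividing the difference in costs by the difference in quality-adjusted life-years (QALYs) between the groups". Net monetary benefit is willingness to pay times the QALY difference, minus costs. Uncertainty in the DCER comes from a bootstrap with 1000 replications. Adjustment for baseline utility is neither mentioned nor excluded.

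**The concern.** Two things stand out, both confined to secondary and economic outcomes.

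First, at months 12 and 18 the same PASI contrast is tested once without and once with the baseline value. The article does not say which result answers the secondary objective. If the two disagree, the choice is open after the data are seen, and the option of a nonparametric test adds a further branch. At months 3, 6, 9 and 15 only the test without the covariate is given as a visit comparison, although the plan explains in the next sentence why the covariate helps.

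Second, the QALY difference is expected to be small: the article anticipates non-inferiority and allows for at most a small loss of effect. A small difference in the denominator of a ratio is sensitive to chance imbalance in baseline utility. Randomization is stratified by biologic only, so balance in utility is left to chance. The same imbalance passes into net monetary benefit, multiplied by the willingness to pay.

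**Working it through.** **No figure to reproduce.** The article gives no SD, correlation or power for PASI or QALYs. Its sample size (222, inflated to 244) concerns the binary primary outcome and does not bear on this point.

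**Inputs from the article**

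- Arms: 162 DR and 82 UC (Power and sample size analyses). The randomized numbers fit here because the article ties the cost-effectiveness analysis to intention-to-treat.
- Seven visits: baseline and months 3, 6, 9, 12, 15 and 18, with the cost-effectiveness questionnaires completed at these visits (Procedures and outcome measures).
- Baseline PASI limited to 0 to 5 (Inclusion criteria).

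**Assumptions, not in the article**

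- Utility SD 0.10 to 0.20, the same at every visit.
- Correlation r between baseline and follow-up: 0.3 to 0.7. For the QALY variance, the same r between any two visits (compound symmetry).

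**PASI.** Adjusting for baseline multiplies the SE of a visit contrast by √(1 − r²):

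| r | SE factor |
|---|---|
| 0.2 | 0.98 |
| 0.3 | 0.95 |
| 0.5 | 0.87 |
| 0.7 | 0.71 |

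The planned ANCOVA already secures this at months 12 and 18, so the unused gain lies at months 3, 6, 9 and 15. The narrow range of baseline PASI may keep r, and hence the gain, low.

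**Chance imbalance in baseline utility.** SE = SD × √(1/162 + 1/82) = SD × 0.1355. This is 0.0136 at SD 0.10 and 0.0271 at SD 0.20.

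**Carry-over into the QALY difference.** With visits 0.25 years apart, the trapezium rule puts weight 0.125 on baseline, 0.25 on each of five intermediate visits and 0.125 on month 18, in total 1.5. The later visits together weigh 1.375. An imbalance at baseline is therefore expected to enter the QALY difference with factor 0.125 + 1.375r:

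| r | Factor | SE, SD 0.10 | SE, SD 0.20 |
|---|---|---|---|
| 0.3 | 0.5375 | 0.007 | 0.015 |
| 0.5 | 0.8125 | 0.011 | 0.022 |
| 0.7 | 1.0875 | 0.015 | 0.029 |

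At SD 0.15 and r = 0.5 the 95% range is ±1.96 × 0.0203 × 0.8125 = ±0.032 QALY.

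**SE of the QALY difference with and without adjustment.** The sum of squared weights is 2 × 0.125² + 5 × 0.25² = 0.34375. In units of the utility variance, the QALY variance is V = 1.5²r + 0.34375(1 − r). Adjustment removes (0.125 + 1.375r)²:

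| r | V | Removed | SE factor | SE at SD 0.15, before → after |
|---|---|---|---|---|
| 0.3 | 0.916 | 0.289 | 0.83 | 0.0195 → 0.0161 |
| 0.5 | 1.297 | 0.660 | 0.70 | 0.0232 → 0.0162 |
| 0.7 | 1.678 | 1.183 | 0.54 | 0.0263 → 0.0143 |

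The SE factor does not depend on the SD.

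**The case against.** The strongest reply is that the adjusted analysis is already in place where an objective asks for it. Months 12 and 18 have ANCOVA. The mixed analysis answers a different objective, the course of PASI. The visit-wise tests are introduced as an addition. This stands: a reader might infer that PASI is analyzed only without adjustment, or that month 12 and 18 PASI is tested in three rival ways, and the article supports neither. Only the t test and the ANCOVA overlap, at two visits. What remains is that neither is named as governing.

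For QALYs, a reader might infer that the plan fixes a raw difference in means. It does not. An adjusted difference also fits the wording, and a condensed article may leave covariates to an analysis plan that is not shown. The point is therefore put as an available improvement and not as an omission.

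Nor is validity at stake. Over repeated randomizations the unadjusted difference is unbiased, and the bootstrap reflects the variation due to chance imbalance. It does so through wider uncertainty, however, and leaves the realized point estimate uncorrected. A DCER with a near-zero denominator stays unstable even after adjustment. The article already adds a scatter plot, a willingness-to-pay curve and net monetary benefit, which does not divide by the QALY difference. These limit the harm but use the same QALY difference.

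Finally, multiplying the baseline imbalance by the full 1.5 years gives an SE of 0.020 to 0.041 QALY. That presumes the imbalance persists undiminished at every visit and contradicts correlations of 0.3 to 0.7, so it should not be used.

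**Conclusion.** The point holds as an improvement at almost no cost to secondary and economic outcomes; the primary outcome is unaffected.

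For PASI, the firmer part is the possibility of competing p-values at months 12 and 18 with no ruling analysis. The loss of precision at the other four visits is real but may be modest.

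For QALYs, chance imbalance in baseline utility would enter an unadjusted difference with an SE of about 0.007 to 0.029 QALY. If the true difference is near zero, that can change the sign and size of the DCER denominator. Adjustment would cut the SE of the difference by about 17% to 46% (factors 0.83 to 0.54).

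These sizes rest on the assumed SD and correlations, on compound symmetry, and on 162 and 82 patients with complete utilities. The documents do not support calling the planned comparisons biased or invalid.

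**What to change.** 1. State that the baseline-adjusted ANCOVA governs PASI at months 12 and 18.
2. Replace the visit-wise t tests with baseline-adjusted visit contrasts, or keep them and label them descriptive.
3. Within each bootstrap replicate, estimate the QALY difference by regression on arm and baseline EQ-5D-5L utility, adding biologic as the stratification factor where numbers allow. Use that estimate in the DCER and in net monetary benefit.

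The cost is slight extra analysis work and some modelling assumptions for skewed scores. No new data are needed, since baseline PASI and EQ-5D-5L are already collected.

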Whether participants will have successful DR after 12 and 18 months, defined as using a lower dose than the normal dose and PASI ≤ 5.Psoriasis disease activity, measured with the Psoriasis Area and Severity Index (PASI) at each 3-monthly study visit. The PASI is a composite measure of erythema, scaling, induration, and extensiveness of the psoriasis plaques [28]. It results in a single score for psoriasis severity ranging from 0 to 72 with lower scores indicating lower disease activity.Dermatology-related quality of life as measured with the Dermatology Life Quality Index (DLQI) at each 3-montly study visit. The DLQI is a practical questionnaire for routine clinical use and consists of 10 questions surveying the impact of skin disease on health-related quality of life. A total sum score ranging from 0 to 30 is derived from all questions, with lower scores indicating limited impact on disease-related quality of life [23].Whether participants will have short disease flares throughout the study period (18 months), defined as a PASI > 5 at one time point.Whether other anti-psoriatic medication will be initiated in participants during the study period (18 months). Investigators will report start of other medications at every study visit.Whether participants will have serious adverse events (SAE) and adverse events of special interest (AEoSI) during the study period. AEoSI include, but are not limited to, infections, malignancies, and joint complaints or new-onset psoriatic arthritis. All adverse events reported spontaneously by the participant or observed by the investigator will be recorded in the CRF during the study period (18 months).Drug trough levels of each included drug will be measured in blood serum samples which will be collected from participants at each 3-montly time point. Serum samples will be analyzed through an enzyme-linked immunosorbent assay (ELISA) for serum drug and anti-drug antibody levels.Anti-drug antibody levels of each included drug will be measured in blood serum samples which will be collected from participants at each 3-montly time point. Serum samples will be analyzed through an enzyme-linked immunosorbent assay (ELISA) for serum drug and anti-drug antibody levels.Utilities will be derived from EuroQoL 5 Dimensions (EQ-5D-5L) questionnaires, which will be measured at each 3-montly time point. The EQ-5D-5L questionnaire consists of 5 dimensions (mobility, self-care, usual activities, pain/discomfort and anxiety/depression), and each dimension has 5 levels: no problems, slight problems, moderate problems, severe problems, and extreme problems. In addition, patients are asked to complete a visual analog scale to rate their health status at a scale of 0–100 [25]. Utility scores will be used to calculate quality-adjusted life years (QALYs) which are used to determine cost-effectiveness of DR.Health status of participants will be assessed by using the Short Form 36 (SF-36) version 2 questionnaire at every 3-monthly time point. The SF-36 consists of 36 questions regarding 8 domains of health, including physical functioning, physical role, pain, general health, vitality, social function, emotional role, and mental health [26, 29]. Scores from all domains will be summarized with differing weightings to calculate mental component scores (MCS) and physical component scores (PCS). Utilities will be derived as well from the SF-36 for sensitivity analyses, calculated based on the 12 specific SF-36 questionnaire answers included in the SF6D system.Volumes of care, as measured with the iMTA Medical Consumption Questionnaire (MCQ) at each 3-monthly time point. The iMTA MCQ measures all relevant health care related costs like outpatient visits at any medical specialist, hospitalizations, and imaging procedures [27]. Scores will be used to calculate direct medicals costs and non-medical costs.Loss of productivity and presenteeism of participants, as measured with the iMTA Productivity Cost Questionnaire (PCQ) at each 3-monthly time point. The iMTA PCQ measures patient-reported absences from paid or unpaid labor [30]. Scores will be used to calculate direct medicals costs and non-medical costs.

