### Power and sample size analyses

The primary outcome is non-inferiority of persistent flares (PASI > 5 for ≥ 3 months) in the intervention group with a non-inferiority margin of 15%. If the upper limit of the 95% confidence interval of the difference in persistent flares between the intervention group versus control group exceeds 15% at 18 months of follow-up, it must be concluded that non-inferiority could not be demonstrated for DR [36]. A margin of 15% was chosen based on clinical grounds, and on previous DR studies [8, 37]. Inherent to the intervention, there could be a small increase in disease flares (i.e., loss of disease control) as drug dosages are lowered. However, it is expected, based on other studies [8, 35], that most flares will be easy to control in the end without residual damage for patients, for example by reintroduction of a higher dose or switch to another biologic. It is therefore expected that persistent flares will not occur very frequently, as has also been shown in the CONDOR trial [8]. In addition, in the UC arm, there will be disease flares as well, as PASI scores might fluctuate over time and some patients might experience loss of effectiveness of their biologic [38]. The chosen non-inferiority margin of 15% is to some extent arbitrary, but refers to a clinically acceptable difference in persistent flares. Of note, the point estimate should be much lower than the margin of 15%, because the margin refers to the upper limit of the 95% confidence interval of the difference in persistent flares which should not exceed 15%. Therefore, we found a margin of 15% (hence a point estimate << 15%) for the difference in persistent flares acceptable, especially because we know that effectiveness could often be regained in patients with persistent flares in studies on other biologics [8, 35]. With an expected chance of being able to reduce biologic dosages in > 50% of patients [8], the benefit-harm ratio seems well balanced by accepting this anticipated increase of persistent flares in patients undergoing DR compared to UC.

With this margin, one-sided testing (*α* = 0.025; 1 − β = 0.8) and a randomization ratio of 2:1 DR versus UC, we calculated that 222 patients need to be included to reject the null-hypothesis of inferiority. Taking a drop-out rate of 10% into account, 244 patients need to be included, with 162 in the DR arm and 82 in the UC arm.

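### The safety objective compares the number of SAEs and AEoSI, but the only named test, Fisher's exact test, compares the proportion of patients affected

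*Protocol article*

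**What the plan says.** Three places in the protocol article describe the safety comparison, in different units.

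- **Secondary objectives** works in events: "To count and compare the number of serious adverse events (SAE) and adverse events of special interest (AEoSI) in patients with DR versus UC". It adds that "AEoSI include, but are not limited to, infections, malignancies, and joint complaints or new-onset psoriatic arthritis". Infections and joint complaints can occur more than once in a patient over 18 months.
- **Procedures and outcome measures**, in the list of secondary outcomes, works in patients: "Whether participants will have serious adverse events (SAE) and adverse events of special interest (AEoSI) during the study period".
- **Statistical analyses** covers both units in its estimates: "Proportions, rate ratios, and relative rate ratios, with corresponding confidence intervals, of SAEs and AEoSI will be described". For testing it names one method, saying that these estimates "of SAEs and AEoSI will be described and differences between groups will be tested using classical statistical methods (Fisher exact test").

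The section does not say whether the test is applied to patients or to events, or how repeat events in one patient enter the rate ratios and their intervals. It also makes observation time unequal. Patients lost to follow-up count only up to the date of loss. Patients on a lower dose who should have gone back to a higher one leave the per-protocol analysis from that deviation onward.

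**The concern.** A comparison of event numbers needs a method that uses every event, allows for patients who have several, and accounts for time observed. Fisher's exact test on patients with at least one event does none of these. A patient with one infection and a patient with five look the same to it, as do a patient followed for 4 months and one followed for 18.

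Two things are at stake. First, the p-value beside the safety results would answer the per-patient question, while the stated objective is the event question. For recurrent AEoSI the event question may be the more sensitive one, in either direction. That matters because the Discussion names a lower risk of side effects as a possible benefit of DR. Second, the deviation rule can shorten observed time only in patients on a protocol-reduced dose, that is, in the DR arm. A yes/no comparison without person-time would then tend to favour DR in the per-protocol analysis. The intention-to-treat sensitivity analysis keeps those patients' data.

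**Working it through.** **Inputs from the document.** "244 patients need to be included, with 162 in the DR arm and 82 in the UC arm"; this agrees with 222 × 1.10 = 244.2 and 162 + 82 = 244. Follow-up is 18 months. The stated alpha and power belong to the primary outcome. No safety event rate, effect size, alpha or power is given, so there is no safety figure to reproduce.

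**Assumptions.** Two-sided 5% level. Event counts per patient over 18 months are Poisson with gamma-distributed variation between patients: UC mean m0, DR mean m1 = RR × m0, dispersion k (k = 0 means no clustering; shape = 1/k). All patients have equal follow-up, so the figures exclude any effect of the cut-offs described above.

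**Worked case: m0 = 1, k = 1 (shape 1), RR = 1.5, so m1 = 1.5.**

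1. Rate analysis with patient-level variance. Var(log RR) = (1/m1 + k)/162 + (1/m0 + k)/82 = 1.667/162 + 2/82 = 0.0103 + 0.0244 = 0.0347, so SE = 0.186. z = ln(1.5)/0.186 = 0.4055/0.1862 = 2.18. Power = Φ(2.18 − 1.96), about 59%. Simulation gives 58%.
2. Patients with at least one event. With k = 1 the proportion is 1 − 1/(1 + m): 0.50 in UC and 0.60 in DR. SE = √(0.24/162 + 0.25/82) = 0.0673. z = 0.10/0.0673 = 1.49. Power = Φ(1.49 − 1.96), about 32%. Fisher's test is somewhat conservative, and simulation gives 29%.
3. In the other direction, RR = 0.67, simulation gives 28% for Fisher and 52% for the rate analysis.
4. All events treated as independent, no true difference. The variance is understated by the factor 1 + k·m = 2. The false-positive rate is P(|Z| > 1.96/√2) = P(|Z| > 1.386), about 17%. Simulation gives 16%. With k = 0 the factor is 1 and simulation gives about 4%.

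**Range.** Simulation at 162 versus 82 with 4,000 trials per setting. Power is for RR = 0.7 over k = 0 to 2. The gap compares the two methods at the same k.

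| UC mean over 18 months | Power, Fisher per patient | Power, rate analysis | Gap, points | False positives if events taken as independent: k = 0 / 1 / 2 |
|---|---|---|---|---|
| 0.1 | 0.09–0.12 | 0.11–0.13 | 1–2 | 0.05 / 0.05 / 0.06 |
| 0.3 | 0.14–0.22 | 0.20–0.27 | 5–6 | 0.04 / 0.08 / 0.10 |
| 0.75 | 0.17–0.38 | 0.30–0.55 | 13–19 | 0.04 / 0.13 / 0.22 |
| 1.5 | 0.14–0.50 | 0.35–0.85 | 22–34 | 0.05 / 0.20 / 0.31 |
| 2.25 | 0.13–0.48 | 0.38–0.95 | 25–47 | 0.05 / 0.27 / 0.39 |

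Under no difference, per-patient Fisher rejects in 3.4% to 4.6% of trials and the rate analysis in about 4% to 6%. Both therefore hold their level approximately, and the gap is one of power and of the question answered.

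**The case against.** The strongest reply is that the listed outcome is per patient, and for that outcome Fisher's exact test is standard and valid. This stands, and the fix keeps the test.

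The second reply is that an event-level comparison is already planned, because the same sentence promises rate ratios with confidence intervals. This also stands. A reader might infer that the plan would hide a difference in infection burden. It would not, because the rate ratio would still show it. What is lacking is a test that belongs to that rate ratio.

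A reader might also infer that the plan over-rejects, by applying Fisher's test to event totals as if events were independent. The document does not support this. Nowhere does it say that the test is run on event totals, its other use in the same section is for proportions of patients with a persistent flare, and the inflation disappears without clustering. The independent-events figures therefore apply only if the rate-ratio intervals or tests are computed that way and events do cluster.

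Finally, the choice of count model is often left to an analysis plan, which is not shown here. That would excuse silence. Here, however, the article names one test for a comparison whose objective is stated in event numbers, and that test does not address event numbers.

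**Conclusion.** The objective (number), the outcome (whether) and the named test (proportion of patients) do not line up, and the number of events has no fitting test. At assumed recurrent-event rates of about 0.5 or more per patient over 18 months, the per-patient test gives up roughly 7 to 50 points of power against a rate analysis. The loss depends on the event rate, the between-patient variation and the direction of the effect. At about 0.1 events per patient, as for rare SAEs or malignancies, the two methods barely differ and both have little power. Intervals that treat events as independent would be too narrow only with clustering.

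The mismatch itself can be read from the text. Its size rests wholly on assumed rates and variation. Safety is a secondary objective, so the non-inferiority conclusion does not depend on it. Label: cheap improvement.

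**What to change.** In Statistical analyses, split the safety analysis by unit.

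1. **Proportion of patients with at least one SAE or AEoSI:** keep Fisher's exact test.
2. **Number of SAEs and of AEoSI:** take the DR/UC rate ratio, its 95% CI and its p-value from one negative binomial model, or one Poisson model with patient-level robust variance, with log follow-up time as offset. Follow-up ends where the patient leaves the analysis in question.
3. **Too few events to fit the model:** report the proportion only.

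Align Secondary objectives and the secondary outcome list so that each names both quantities.

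The cost is a sentence or two of wording and one extra model. Adverse events are already recorded throughout the 18 months, and the dates of deviation and loss are already needed for the per-protocol analysis. The one downside for the results is wider rate-ratio intervals where events cluster within patients, which is the honest width.
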